## Methods

The study is registered with the US National Institutes of Health clinical trials registry (ClinicalTrials.gov Identifier: NCT04237519). This trial report follows the recommendations of SPIRIT 2013 [44].

### Efficacy trial

#### Design

The design of the efficacy trial and adherence sub-study is illustrated in Table 1. The efficacy trial will be a double-blind parallel group multicentric RCT. It will be completed in three sites: Centre Leenaards de la mémoire – Centre hospitalier universitaire Vaudois (CHUV) in Switzerland; Institut universitaire de gériatrie de Montréal (IUGM) of the Centre intégré universitaire de santé et de services sociaux Centre-Sud-de-l’Île-de-Montréal (CIUSSS-CSMTL) in Canada; and Brusano and Centre Public d’Action Sociale (CPAS) of Woluwe-Saint-Lambert in Belgium. Participants will be randomised to one of two home-based computerised intervention conditions, the StayFitLonger training programme (experimental) or the comparator, an active control training programme. Outcome measures (Table 2) will be collected at two timepoints: pre-training (T0; within 6 weeks prior to the start of the intervention) and post-training (T1, within 4 weeks following the end of the 26-week training). Of note, a second exploratory post-training assessment (T2), not part of the RCT, will be performed within 4 weeks following the end of the adherence sub-study. At each timepoint, there will be two assessment visits. Within a month following the T0 assessment, introductory courses in groups of a maximum of six people will take place to introduce the features of the programme and describe the different physical and cognitive exercises. This will mark the beginning of the training that will take place at home for 26 weeks (see Table 1 for details). Participants will be supervised through home visits and monthly phone calls to monitor their use in relation to recommendation and address problems with the use of the programme.

**Table 1 Tab1:**
[figure not shown]
Schedule of enrolment, assessments and interventions

**Table 2 Tab2:** List of outcomes measured for the RCT

RCT Outcomes				Timepoints		
***Domain***	***Primary outcome***			T0	T1	T2^a^
Physical	Mobility/gait	Timed-Up & Go (TUG) task		X	X	X
***Domain***	***Secondary outcomes***					
Physical	Mobility/balance	20-m Walking task		X	X	X
		Five Time Sit to Stand Test		X	X	X
		Four Stage Balance Test		X	X	X
		Gait Up sensor measurements: several walking parameters		X	X	X
Cognitive	Global cognition: ZAVEN Composite Score	Episodic memory composite	California Verbal Learning Test (CVLT): free delayed recall	X	X	X
			Wechsler Memory Scale (WMS-IV) Logical Memory Test: delayed recall	X	X	X
		Complex attention composite	Wechsler Adult Intelligence Scale (WAIS-IV) Digit Symbol Substitution Test (DSST)	X	X	X
		Executive function composite	Verbal Fluency task	X	X	X
	Memory Composite Score	CVLT: free delayed recall		X	X	X
		WMS-IV Logical Memory Test: delayed recall		X	X	X
	Executive and attentional functions Composite Score	Verbal Fluency test		X	X	X
		Trail Making Test: Part B- Part A		X	X	X
		Victoria Stroop Test (VST): high interference		X	X	X
		Test of Attention Performance (TAP): Divided Attention		X	X	X
	Speed processing Composite Score	Trail Making Test: Part A		X	X	X
		WAIS-IV DSST		X	X	X
		VST: “naming” condition		X	X	X
	Divided attention	Ad-hoc computerised multitasking task		X	X	X
	Prospective memory	Prospective memory items of the Rivermead Behavioural Memory Test (RBMT-3)		X	X	X
	Concept elaboration	Test of Attention Performance (TAP): Flexibility		X	X	X
		WAIS-IV Similarities		X	X	X
Affective	Mood	Hospital Anxiety and Depression Scale (HADS)		X	X	X
	Fear of falling	Falls Efficacy Scale International (FES-I)		X	X	X
Psycho-social	Quality of Life	The Older People Quality of Life questionnaire (OPQOL 35)		X	X	X
	Subjective difficulties encountered in activities of daily living	Cognitive Function Instrument (CFI)		X	X	X
		Everyday Cognition (E-Cog)		X	X	X
	Expectation questionnaire	Ad-hoc questionnaire on participant’s expectation on the programme		X	X	X

^a^T2 assessment is listed here but it is not technically part of the RCT

#### Study population

One hundred and twenty-eight French-speaking healthy participants will be recruited, 64 in Switzerland, 32 in Canada and 32 in Belgium. Participants will be community-dwelling older adults. They will be recruited through diverse sources including ads, newsletters, social media, and flyer distribution during various events. Recruitment will be carried out with the help of two community associations, Pro Senectute in Switzerland and Brusano in Belgium, and from the bank of participants of the IUGM research centre in Canada.

##### Inclusion criteria

Included participants will be fluent French-speaking adults aged 60 years and over, retired and living at home. They will have access to a wireless Internet connection at home and will be open to the use of new technologies including electronic tablets. They will be independent for daily activities based on a normal score on the 4-Instrumental Activities of Daily Living (4-IADL) scale [45]. They will be interested in exercising to stay fit and able to walk at home without a walking aid (e.g., wheelchair, cane, walker, etc.). They will be available to commit themselves for the time period during which the study will take place, with no vision deficits that would prevent them to read information on a tablet and with no current neurological or psychiatric diagnosis (e.g., Parkinson’s disease).

##### Exclusion criteria

Participants with a MoCA score < 26 [46] or a score ≥ 3 on the Fried’s frailty index [2] will be excluded from the study.

#### Procedure and data management

A two-stage screening process will be used to select participants (timepoint T-1; Table 1). Initial contact will be made by phone by research team members with expertise in recruitment. At this stage, only participants who report no major physical, medical, or sensory limitations will be invited to come to the laboratory for further investigation. During the on-site visit, participants will be presented with the information and consent form. In Switzerland, participants will be offered to receive the information and consent form prior to their visit. Once they sign the consent form, inclusion and exclusion entry criteria will be measured for the second-stage screening. The Fried’s phenotype scale [2] will be used to exclude frail individuals and to determine frailty level among other participants who will be identified as either robust (score of 0) or pre-frail (score of 1 or 2). In addition, the participant’s technology (e.g., use of tablet, email, social network) and gaming profile will be established with an ad-hoc questionnaire. Eligible participants will receive an ID number. All data will be anonymized and maintained in REDCap, a secure online database [47]. Access to data will be restricted by type of data (e.g., assessors will only have access to assessment data). Furthermore, data collected directly by the programme will be transmitted and maintained in a secured server located at the Haute École Spécialisée de Suisse Occidentale (HES-SO).

#### Randomisation and blinding procedure

A randomisation list will be generated in Switzerland, independently from the research project and implemented using REDCap. In each site, a team member not involved in assessment or monitoring will assign participants by pressing a “randomisation” button on REDCap. A stratification will be done according to the frailty status. Within each stratum (robust and pre-frail), participants will be assigned to one of the two conditions (StayFitLonger or active control) according to separate randomisation schedules with a 1:1 ratio. Couples (e.g., married individuals) who participate in the study will be assigned to one of the two conditions as a pair: the first member of the couple will be randomised, and the second will be assigned to the same intervention. This has been implemented to avoid contamination in cases where two individuals living in the same household would be randomized to different training programmes.

Assessors will be blind to the hypotheses and to participants’ assignment, as they will only have access to the testing sessions. Participants will be asked not to discuss their training programme with assessors. If such a circumstance were to occur, it will be reported but should have minimal effect on data integrity, as assessors will be blinded to the hypotheses. Research team members responsible for the statistical analyses will be blind to the training conditions. Study coordinators and instructors involved in the introductory courses and supervision of home-based training will not be blind. Participants will be aware that the trial has two different training conditions and that they will be randomly allocated to one of them. However, they will not be informed of the study hypotheses and therefore will not know which one is the experimental condition. Both programmes will have a similar main screen layout and name, and the wording of the recruitment documents and consent forms will not convey the notion that one condition is hypothesised as inferior in terms of its effects on physical capacities and cognition [48].

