#### Statistical analyses

##### Sample size calculation

Given that our secondary analyses will stratify participants into two categories (robust and pre-frail), we determined our sample size to ensure that we have the capacity to test the hypotheses related to this stratification. This was done with a Marker Stratified Design using the following plan: marker-by-treatment interaction using separate test (see: http://www.bigted.org/NonAdaptiveDesigns/MarkerStratifiedDesigns.html). For pre-frail participants, it was estimated that 16 participants per group (StayFitLonger vs. active control) would be required to detect a significant difference of 3.22 s in the TUG test using a two-sided t-test (alpha = 0.05) based on the T&E pilot study. As data might not be normally distributed, a non-parametric test was required resulting in a sample size of about 18 participants per group. Considering a dropout rate of about 25% based on prior studies, a sample size of 24.5 pre-frail participants should be enrolled for each group. For robust older adults, a sample size of 23.5 participants per group would allow to detect a difference of 0.82 s on the TUG test using a two-sided t-test (alpha = 0.05) with a power of 80% based on the study by Uemura et al. [77]. By accounting for the non-normality of data (using a non-parametric test) and the dropout rate, we targeted recruiting 36 robust participants per group. Thus, a total sample of 122 participants was determined as sufficient to have the appropriate power based on sample size calculation. To have a balanced distribution in the three countries, the total N targeted for recruitment was set at 128 participants.

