##### Analysis of efficacy on primary and secondary outcomes

All statistical tests will be two-tailed and a *p* value < .05 will indicate statistical significance. Effect sizes will also be assessed. Standard descriptive statistics will be provided with means and standard deviation for demographics and baseline characteristics. Group comparisons will be made using t-tests for continuous variables and chi-square analyses for discrete variables.

The primary efficacy analysis will be done with a modified intention-to treat (mITT) approach. All participants will be included in the analyses and the characteristics of those who withdrew will be analysed, as well as the causes leading them to leave the study. A linear mixed model will be used to analyse the data, as it handles correlated data and unbalanced designs and are robust against missing values. The fixed effects will be Intervention (StayFitLonger vs. active control), Time (T0, T1) and their interaction. If the StayFitLonger training is more beneficial than the active control training, a significant interaction will be expected. In such case, the presence of a significant difference between T0 and T1 in each group will be evaluated, as well as group difference on change scores at post-training using the pre-training and control group as reference points. The same analysis will be used with primary and secondary outcomes. To examine the effect of frailty status on efficacy, participants will be stratified into robust and pre-frail seniors and data will be analyzed separately in these two populations using the same method described above.

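### Couples are allocated as one unit, but the sample size and the stated analyses make no allowance for it, and the timing of the second partner's enrolment is left open

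*Protocol article*

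**What the plan says.** The Randomisation and blinding procedure section stratifies by frailty ("A stratification will be done according to the frailty status") and allocates within each stratum "according to separate randomisation schedules with a 1:1 ratio". Couples are an exception: they "will be assigned to one of the two conditions as a pair", meaning that "the first member of the couple will be randomised, and the second will be assigned to the same intervention". The stated reason is to avoid contamination within a household. Allocation is done at each site, where "a team member not involved in assessment or monitoring will assign participants by pressing a “randomisation” button on REDCap". On who knows the arm afterwards: "Study coordinators and instructors involved in the introductory courses and supervision of home-based training will not be blind".

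The Sample size calculation section works from two-sided t-tests in each frailty stratum, inflated for a non-parametric test and for dropout, and concludes that "a total sample of 122 participants was determined as sufficient to have the appropriate power". The recruitment target is 128. Couples are not mentioned.

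The section on efficacy analysis names a linear mixed model, justified partly by its ability to handle correlated data. "The fixed effects will be Intervention (StayFitLonger vs. active control), Time (T0, T1) and their interaction". No random effects are listed, and no couple or household term appears.

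**The concern.** The pairing rule is sensible in itself, but it creates clusters of two that the rest of the plan does not carry forward. Partners share a household and often habits, so their changes in TUG may be more alike than those of two unrelated people in the same arm. If so, an analysis that ignores the pairing overstates the information in the data. Standard errors for the primary contrast and for the secondary contrasts would be too small, and the sample size would be slightly short.

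A separate point concerns enrolment. Once the first partner is randomised, the second partner's arm is certain. If the second partner has not yet consented and been screened, the household and the unblinded coordinators could know that arm beforehand, and the decision to enrol could depend on it. Blinded assessors do not protect against selection at that step.

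**Working it through.** **1. The plan's own figure.** The per-group starting values are 16 (pre-frail) and 23.5 (robust). An assumed non-parametric factor of 1.15, followed by division by 1 - 0.25 for dropout, reproduces the stated figures:

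- Pre-frail: 16 × 1.15 = 18.4; 18.4 / 0.75 = 24.5.
- Robust: 23.5 × 1.15 = 27.0; 27.0 / 0.75 = 36.0.
- Total: 2 × 24.5 + 2 × 36 = 121, or 2 × 25 + 2 × 36 = 122 after rounding up.

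So 122 is reproduced, and no factor in the chain allows for couples. The starting values cannot be checked, because the article gives no standard deviation.

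**2. Design effect.** Let f be the share of participants who belong to a couple and ρ the within-couple correlation of TUG change. The size-weighted mean cluster size is 2f + (1 - f) = 1 + f, so

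DE = 1 + (1 + f - 1) × ρ = 1 + fρ.

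Neither f nor ρ is in the documents; both are assumed.

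**3. Consequences.**

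- Type I error if pairing is ignored: 2[1 - Φ(1.96/√DE)].
- Power at fixed size, if nominally 80%: Φ((1.96 + 0.84)/√DE - 1.96).
- Required total: 122 × DE.

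| f | ρ | DE | Type I error | Power | Required total |
|---|---|---|---|---|---|
| 0.1 | 0.05 | 1.005 | 5.1% | 79.8% | 122.6 |
| 0.1 | 0.5 | 1.05 | 5.6% | 78.1% | 128.1 |
| 0.2 | 0.1 | 1.02 | 5.2% | 79.2% | 124.4 |
| 0.2 | 0.3 | 1.06 | 5.7% | 77.7% | 129.3 |
| 0.3 | 0.3 | 1.09 | 6.1% | 76.5% | 133.0 |
| 0.3 | 0.5 | 1.15 | 6.8% | 74.3% | 140.3 |

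In head counts, 20 couples are 40 of 128 people (f = 0.3125). With ρ = 0.5, DE = 1.156 and type I error is again about 6.8%.

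**4. Simulation.** An unadjusted two-sample comparison of change with 96 completers (128 × 0.75) rejected in 5.0% of null trials with no couples, 5.4% at f = 0.2 and ρ = 0.1, and 6.3% at f = 0.3 and ρ = 0.3. This agrees with the formula to within a few tenths of a point.

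**5. What the spare recruitment covers.** 128/122 = 1.049, so the target absorbs a design effect up to fρ = 0.049. At f = 0.3 that means ρ up to about 0.16. The margin protects power only; it does not correct a standard error that ignores pairing.

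**6. Which term would help.** The treatment effect is the Intervention × Time interaction, a contrast in change from T0 to T1. A household intercept that is constant over time drops out of T1 - T0, exactly with complete data and largely otherwise. Only correlation between partners' changes matters, so a plain household intercept would not address it.

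**The case against.** The strongest reply is that the article never says partners are analysed as independent. It lists fixed effects only, with not even a participant-level random effect, and says that mixed models handle correlated data. A household term would belong with the random effects or the covariance structure, which an article may leave to the full protocol or analysis plan. This stands: a reader might infer that the mixed model ignores pairing, but the text does not establish it. The t-tests and chi-square tests in the same section do assume independent people, but they follow the sentence on baseline characteristics and carry little weight for efficacy. What remains is the sample size, which visibly makes no allowance, and a model description that names no such term.

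A reader might also infer that concealment is lost for second partners. The documents do not support that. Nothing says that second partners enrol later, and the wording is compatible with both being enrolled before the pair is allocated. The person who randomises takes no part in assessment or monitoring, and participants are not told which programme is experimental. All the article shows is that no rule on timing is stated.

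Two further points stand. Sharing a programme does not itself create residual correlation, because everyone in the arm shares it and the intervention term takes it up; only household-specific similarity in change counts. And placing the second partner outside the frailty-stratified schedule affects balance within strata, not validity, since frailty is still measured on each person.

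**Conclusion.** The point holds in a limited form. The trial creates a unit of randomisation that its sample size ignores and its stated analyses do not mention. If partners' changes are positively correlated and no suitable term is used, standard errors are too small by a factor of √DE, which is about 1.003 to 1.07 over f = 0.1-0.3 and ρ = 0.05-0.5. Type I error is then about 5.1-6.8%, and 80% power falls by between 0.2 and 5.7 points. The lower part of this range is covered, as far as power goes, by recruiting 128 rather than 122. All of these figures rest on assumed values of f and ρ. The effect is small unless couples are common and strongly alike.

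In the separate frailty analyses, only couples whose members fall in the same stratum are clustered, so the size there depends on a further number that is not given.

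The enrolment point is an open procedural risk and has no numerical size.

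**What to change.** - **Analysis.** State that the primary and secondary models use household-clustered robust standard errors, with each single participant as their own household. A household-by-time random effect is the alternative, but may be poorly estimated with few couples. A plain household intercept is not enough.
- **Sensitivity.** Repeat the primary analysis keeping only the first-randomised partner of each couple. This also addresses any arm-dependent enrolment of second partners at sites that have already recruited.
- **Reporting.** Give the number of couples by arm and by frailty stratum.
- **Procedure.** Complete consent, eligibility and frailty screening for both partners before the couple is randomised, and state which partner's stratum applies when the two differ. The Trial status section says that recruitment is complete in Switzerland and Canada, which account for 64 + 32 = 96 of the 128 planned. This rule can therefore reach only the remaining Belgian participants, at most 32.

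The cost is one line in the analysis specification, one line in the site procedure, and slightly wider intervals. No change to the recruitment target is needed on this ground unless couples prove frequent.
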